# Effect of a telerehabilitation exercise program versus a digital booklet with self-care for patients with chronic non-specific neck pain: a protocol of a randomized controlled trial assessor-blinded, 3 months follow-up

**DOI:** 10.1186/s13063-023-07651-z

**Published:** 2023-09-28

**Keywords:** Neck pain, Chronic pain, Internet-based intervention, Clinical trial protocol

## Abstract

**Background:**

Neck pain is the fourth worldwide leading cause of disability and represents 22% of musculoskeletal disorders. Conservative intervention has been strongly recommended to treat chronic neck pain and Telerehabilitation is the alternative for the treatment of musculoskeletal conditions. There is a lack of high-quality research on the effects of telerehabilitation in patients with neck pain and functional disability. Therefore, this study aims to evaluate the effect of a telerehabilitation exercise program versus a digital booklet only with self-care information in individuals with non-specific chronic neck pain.

**Methods:**

This is a prospectively registered, assessor-blinded, two-arm randomized controlled trial comparing a telerehabilitation exercise program versus a digital booklet with self-care information. Seventy patients will be recruited with non-specific chronic neck pain. Follow-ups will be conducted post-treatment, 6 weeks, and 3 months after randomization. The primary outcome will be disability at post-treatment (6 weeks) measured using neck pain disability. Secondary outcomes will be pain intensity levels, global perceived effect, self-efficacy, quality of life, kinesiophobia, and adherence to treatment. In our hypothesis, patients allocated to the intervention group experience outcomes that are similar to those of those assigned to the self-care digital booklet. Our hypothesis can then be approved or disapproved based on the results of the study.

**Discussion:**

This randomized clinical trial will provide reliable information on the use of telerehabilitation to treat patients with chronic non-specific neck pain.

**Trial registration:**

The study was prospectively registered at the Brazilian Registry of Clinical Trials (number: RBR-10h7khvk). Registered on 16 September 2022.

## Introduction

Neck (cervical) pain is the fourth worldwide leading cause of disability and represents 22% of musculoskeletal disorders [1, 2]. It is estimated that neck pain affects more than 65 million people annually worldwide — annual incidence remains between 15 to 50% — and 70% of the population is affected throughout life [3]. The Global Burden of Disease 2017 study indicated neck pain as the ninth and eleventh cause of years lived with disability among women and men, respectively [4]. Overall, neck pain can result in significant health costs, including medical expenses, loss of productivity, and costs associated with various treatments. The average annual health costs for individuals with neck pain were US$ 3709 to US$ 2731 for those without neck pain [5]. In the Netherlands, total annual societal costs of neck pain were estimated at US$ 686 million [6].

Chronic non-specific neck pain is restricted to the cervical region without radiation to the upper limbs and symptoms last more than 12 weeks. It can be defined as the pain in the posterior cervical region from the superior nuchal line to the spine of the scapula and the side region down to the superior border of the clavicle and the suprasternal notch [7, 8].

Conservative intervention has been strongly recommended to treat chronic neck pain. Postural and mobility exercises, and cervical (or cervicothoracic) manipulation or mobilizations combined with stretching and strengthening have been found as evidence-based treatments to decrease neck pain and improve range of motion [9, 10]. Cervical exercise is an effective treatment for neck pain [11, 12]. A recent systematic review of patients with chronic neck pain concluded that multimodal training (exercises involving deep and superficial cervical muscles) is necessary to have beneficial effects on function and symptoms [13]. A recent systematic review with meta-analysis showed that motor control, Yoga, Pilates, TaiChi, and strengthening exercises have beneficial effects on neck pain relief when compared with no treatment [14].

Telerehabilitation is the use of communication and information technologies such as telephones, video conferencing, sensors, virtual reality, and robotics to deliver rehabilitation services at a distance [15, 16]. This practical modality is becoming popular among patients with musculoskeletal pain as a solution to healthcare access barriers related to travel conditions (distance, transit, transportation) and high demand (long waiting lists) [17–19]. Recent studies indicate that telerehabilitation can improve accessibility to healthcare services and increase patients’ adherence level to exercise programs due to its flexibility and convenience [20–22]. The feasibility of telerehabilitation protocols to treat hip and knee arthroplasty, non-specific low back pain, rheumatoid arthritis, osteoarthritis, and others have been reported [19, 23, 24]. Furthermore, telerehabilitation has been used in a wide range of fields including musculoskeletal pain [25, 26]. Then, high-quality randomized controlled trials are needed to investigate the effectiveness of telerehabilitation for people with neck pain.

A recent study observed that telerehabilitation is an effective method to improve function and relieve pain in patients with musculoskeletal conditions [27]. The only two studies on the effectiveness of telerehabilitation to treat patients with chronic non-specific neck pain have presented methodological flaws such as lack of evaluator blinding, intention-to-treat analysis, and hidden allocation [28, 29]; hence, studies that follow adequate methods are needed.

Therefore, this randomized controlled trial aims to evaluate the effect of a telerehabilitation exercise program versus a digital booklet only with self-care information (chronic pain, benefits of physical exercise, and healthy lifestyle guidelines) in individuals with non-specific chronic neck pain. The primary outcome will be disability at post-treatment (6 weeks) measured using neck pain disability. Secondary outcomes will be pain intensity levels, global perceived effect, self-efficacy, quality of life, kinesiophobia, and adherence to treatment.

## Methods

### Study design

This two-arm, randomized, controlled, and evaluator-blinded study will be conducted under both the Consolidated Standards of Reporting Trials (CONSORT) [30] and Standard Protocol Items: Recommendations for Interventional Trials (SPIRIT) [31].

### Register and protocol version

The Research Ethics Committee of the Federal University of Pará, Brazil (registration no. 5.458.454), granted approval for this clinical trial. The study adhered to the ethical principles stated in the Declaration of Helsinki for human studies. Additionally, the trial was registered with the Brazilian Registry of Clinical Trials (registration no. RBR-10h7khvk). All co-authors provided their approval for the study.

### Study setting and recruitment procedure

Physiotherapists from the outpatient musculoskeletal physiotherapy department at the Faculty of Physiotherapy and Occupational Therapy, Federal University of Pará, Belem, Brazil, will identify all patients who have been experiencing neck pain for more than 12 weeks and are seeking care for chronic neck pain. If patients express interest in participating, their contact details will be provided to the research team.

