### Potential participants from the general community

To facilitate recruitment from the general community, the study advertising materials and documents will be shared through community channels and social media platforms. This will include, but is not limited to, promotion through social media and online advertising services. The social media strategy will involve sharing the study poster and the study webpage URL on platforms such as Facebook and Instagram.

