### Eligibility criteria

Potential participants will be phoned to determine eligibility before enrollment:18 to 60 years old male or female interested to treat chronic neck pain.Access to the internet via computer/smartphone.Read and understand the Portuguese language.Neck pain for more than 12 weeks [32].

Individuals with severe musculoskeletal disorders, cardiovascular and metabolic disorders, history of neurological injuries, use of muscle relaxants, obesity (body mass index > 30 kg/m^2^), red flags (unexplained weight loss, fever, moderate to severe trauma, among others) [33], cognitive problems, visual or hearing impairments, or any health condition that hinder safe and proper participation in online exercise sessions will be excluded.

The Physical Activity Readiness Questionnaire (PAR-Q) of the Canadian Society of Exercise Physiology will be used to determine the ability of participants to perform physical activities [34, 35].

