### Control group

Participants will receive the same digital booklet with self-care information containing general information about self-management of chronic pain, including pain education, advice on healthy lifestyle and sleeping habits and promotion of physical activity. In addition, participants will receive phone text messages, WhatsApp messages, or e-mails once a week to encourage the maintenance of healthy habits during the study period. The participants will be able to clear doubts through telephone contact. The participants of both groups were instructed not to change any medication prescribed by their physician and not to seek other treatment for their low back pain during the study.

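### Eligibility does not exclude current neck physiotherapy or exercise, and the only concurrent-care instruction names low back pain, so care already under way can dilute the contrast

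*Protocol article*

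**What the plan says.** **Recruitment.** Study setting and recruitment procedure says that physiotherapists of an outpatient musculoskeletal department "will identify all patients who have been experiencing neck pain for more than 12 weeks and are seeking care for chronic neck pain". The next section adds a second source: "To facilitate recruitment from the general community, the study advertising materials and documents will be shared through community channels and social media platforms". The split between the two sources is not given.

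**Eligibility.** The inclusion list opens with "18 to 60 years old male or female interested to treat chronic neck pain" and adds internet access, Portuguese literacy and pain for more than 12 weeks. The exclusions are itemised. The only one that concerns a treatment sits in the run "history of neurological injuries, use of muscle relaxants, obesity". Physiotherapy, manual therapy and exercise for the neck are not mentioned. Eligibility is checked by telephone before enrolment.

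**Concurrent care.** The one rule is under Control group and applies to both arms. It has two parts: "The participants of both groups were instructed not to change any medication prescribed by their physician", and an instruction "not to seek other treatment for their low back pain during the study".

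**Contrast.** The Introduction sets the exercise programme "versus a digital booklet only with self-care information" and states that "Cervical exercise is an effective treatment for neck pain".

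**Baseline data.** Procedure lists demographic, clinical and medical data. Prior or current neck treatment and usual exercise are not among the items named.

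**The concern.** The experimental treatment is exercise for the neck. By the Introduction's own account, exercise works, and so do manual treatments combined with stretching and strengthening. A person partway through a course of in-person neck physiotherapy, or attending a supervised strengthening class for neck pain, meets every criterion as written. If allocated to the booklet, that person receives an active treatment of the same kind as the experimental arm.

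The concurrent-care sentence ought to deal with this, but it falls short in two ways. It names low back pain in a neck pain trial, so read literally it does not restrict neck treatment at all. It also speaks of seeking treatment, which leaves open whether sessions already booked or in progress are covered.

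What is at stake is how clearly the 6-week difference in the Neck Disability Index can be read as exercise against booklet. If background neck care is not recorded by arm, a small observed difference could not be separated into a weak programme and a treated control group.

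**Working it through.** **1. The passages side by side**

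| Situation at entry | Eligibility criteria | Control group instruction |
|---|---|---|
| Uses muscle relaxants | Excluded | Not needed |
| Other prescribed medication | Allowed | To be kept unchanged |
| Neck physiotherapy, manual therapy or supervised exercise under way | Not mentioned, so eligible | Names low back pain; speaks of seeking, not continuing |
| New neck treatment sought during the study | Not applicable | Probably intended, but names low back pain |
| Neck treatment completed shortly before entry | Not mentioned, so eligible | Not covered |

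Neither section settles the third row. It is the row closest to the experimental treatment.

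**2. The plan's own sample size**

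Inputs from Sample size calculation: difference 4.21, SD 5.58, two-sided alpha 0.05, power 80%, dropout 15%.

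n per arm = 2 × [5.58 × (1.960 + 0.842) / 4.21]² = 27.6, rounded up to 28. Allowing for dropout, 28 / 0.85 = 32.9, or 33. The stated minimum is 32 per group, so the figure reproduces to within one participant.

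The Abstract plans 70 participants, which is 35 per arm. After 15% dropout this leaves 35 × 0.85 = 29.75; 29 is used below.

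**3. What background care does to the difference**

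Let f be the fraction of each arm in neck treatment. Let b be the benefit of that treatment over the booklet alone, and a the extra benefit it gives on top of telerehabilitation. The expected difference is then

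(4.21 + f·a) − f·b = 4.21 − f·(b − a).

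The documents give none of f, a or b. Two limiting cases bound the illustration:

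- **a = b** (background care adds equally in both arms): the difference stays at 4.21 for any f.
- **b = 4.21, a = 0** (treated controls gain the whole planned effect, treated telerehabilitation participants gain nothing more): the difference is 4.21 × (1 − f).

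Power = Φ(difference / [5.58 × √(2/29)] − 1.96), where 5.58 × √(2/29) = 1.465.

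| f (assumed) | Difference, a = b | Power | Difference, b = 4.21 and a = 0 | Power |
|---|---|---|---|---|
| 0% | 4.21 | 82% | 4.21 | 82% |
| 10% | 4.21 | 82% | 3.79 | 73% |
| 20% | 4.21 | 82% | 3.37 | 63% |
| 30% | 4.21 | 82% | 2.95 | 52% |

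An intermediate case, with f = 20%, b = 4.21 and a = b/2, gives 4.21 − 0.20 × 2.105 = 3.79, or 73% power.

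The range of f is illustrative. The table shows only that the planned size has little slack if dilution occurs. It does not show that dilution will occur.

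**The case against.** The strongest reply is that nothing in the protocol shows treated patients entering the trial. Seeking care, and being interested in treatment, describe people looking for help and not people already receiving it. The clinic is only one of two sources. Both arms are told about other treatment, and a participant could reasonably take that instruction to cover continuing sessions and to mean the neck. The reference to low back pain may be no more than a slip. A journal article also condenses, and a fuller protocol may hold more detail.

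Much of this stands, and it rules out several stronger readings that a reader might infer:

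- **That ongoing care does enter both arms.** The text shows only that it can.
- **That carry-over from completed treatment biases the comparison.** Allocation is 1:1, random and concealed, so recent treatment is balanced in expectation. The idea that recently treated people have less room to improve has no figure behind it in the documents.
- **That power will fall to 73%, 63% or 52%.** Those values need an undocumented fraction and the assumption that background care adds nothing in the telerehabilitation arm.
- **That the gap steers the trial to a conclusion of similarity.** The Discussion does state a hypothesis of similar outcomes, but it also expects telerehabilitation to prove efficient. The sample size is set to detect a difference, and Statistical analysis commits to estimation.
- **That the control is misdescribed because of background care.** The phrase "versus a digital booklet only with self-care information" names the randomised comparator and does not promise that no other care exists. The weekly messages and telephone contact in the control arm are a separate matter.

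What survives is narrower. The eligibility list is itemised down to body mass index and one drug class, so its silence on neck treatment is what a screener would apply. The concurrent-care sentence is current text, and as written it names the wrong condition for this trial.

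**Conclusion.** The point holds as a gap between two sections. Eligibility criteria admits people currently in neck physiotherapy, manual therapy or supervised neck exercise. The Control group instruction, which refers to low back pain and to seeking treatment, does not clearly cover them. Such care may enter either arm. It is not confounding and does not invalidate the randomised comparison. Its possible effect is dilution, where controls receive treatment of the experimental kind.

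The size is unknown. It runs from no loss, if background care adds equally in both arms, to the reduced power shown above under the least favourable assumption. Neither f nor the added benefit in each arm can be taken from the documents. This is a cheap improvement, not a fault that undermines the trial.

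**What to change.** 1. **Eligibility criteria:** add an exclusion for people currently receiving physiotherapy, manual therapy or supervised exercise for neck pain, asked in the eligibility call already planned.
2. **Control group:** reconcile the concurrent-care sentence with the condition under study, so that it refers to neck pain and covers continuing as well as seeking treatment.
3. **Procedure:** record recent neck treatment at baseline and concurrent neck treatment at both follow-ups, and report them by arm. Any remaining dilution can then be described.

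Whether to add a washout for completed treatment, and how long, is the investigators' choice. It narrows the population and is not needed for a valid randomised comparison.

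The cost is one criterion, one screening question and a few questionnaire items. The clinic pool becomes slightly smaller, and the community recruitment already planned can help make up for that.

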### Potential participants from the general community

To facilitate recruitment from the general community, the study advertising materials and documents will be shared through community channels and social media platforms. This will include, but is not limited to, promotion through social media and online advertising services. The social media strategy will involve sharing the study poster and the study webpage URL on platforms such as Facebook and Instagram.

### Eligibility criteria

Potential participants will be phoned to determine eligibility before enrollment:18 to 60 years old male or female interested to treat chronic neck pain.Access to the internet via computer/smartphone.Read and understand the Portuguese language.Neck pain for more than 12 weeks [32].

Individuals with severe musculoskeletal disorders, cardiovascular and metabolic disorders, history of neurological injuries, use of muscle relaxants, obesity (body mass index > 30 kg/m^2^), red flags (unexplained weight loss, fever, moderate to severe trauma, among others) [33], cognitive problems, visual or hearing impairments, or any health condition that hinder safe and proper participation in online exercise sessions will be excluded.

The Physical Activity Readiness Questionnaire (PAR-Q) of the Canadian Society of Exercise Physiology will be used to determine the ability of participants to perform physical activities [34, 35].

### Procedure

Eligible participants will receive a digital informed consent form and will be informed about the study objectives by a blinded and trained evaluator. Participants will be referred for baseline assessment consisting of the demographic (age, sex, weight, height, marital state, profession, and education level), clinical (comorbidities, duration of pain, location of pain, average pain intensity, pain area) and medical data. The baseline evaluation will be performed via video conferencing, while the 6-week and 12-week follow-ups will be performed via phone call, smartphone text message, or email by using a Google Forms questionnaire (Fig. 1). All data will be encoded and typed twice using Microsoft Excel. A second blinded evaluator will double-check all data before analysis.

**Fig. 1 Fig1:**
[figure not shown]
Study flowchart

### Primary outcome

Disability will be measured through the Brazilian-Portuguese version of the Neck Disability Index [36], which is a 10-item self-administered questionnaire regarding limitations in daily activities due to neck pain. The total score ranges from 0 (no limitations) to 50 (major limitations) [36].

### Randomization and group allocation

The Research Randomizer tool (http://www.randomizer.org/) will be used to generate random numbers and assign the participants to the Telerehabilitation Group and Control Group. Allocation (1:1 ratio) will be performed by an independent researcher without participation in data acquisition and statistical analysis. Concealed allocation will be performed by using sequentially numbered, opaque, and sealed envelopes. The same blinded evaluator will open the sealed envelopes after the informed consent form is filled and perform the participant baseline evaluation. Participants will receive a unique study registration number and will be referred to the physical therapist responsible for each group.

### Data collection and management plan

Participants will be identified by an individual trial number (ID) to ensure confidentiality, coding, and confidentiality. A data management plan will also be designed in accordance with the recommendations and regulations of the Federal University of Pará, Belem, Brazil. The security and confidentiality of the data collected at all stages will be ensured by storing it on password-protected servers. Paper-based data will be kept in locked filing cabinets at the Postgraduate Program in Human Movement Sciences. Access to the data will be restricted to the lead investigator only. All statistical analyses will be performed using the individual number of each participant and the statistician will be blinded to the group. The results will be presented by group data and any individual data will be spread to ensure confidentiality is preserved.

A Data Monitoring Committee (DMC) will be convened to overview data collection and integrity. The DMC will approve the statistical analysis plan and research protocol. The integrity of trial data will be monitored by regularly scrutinizing data sheets for omissions and errors. Data inconsistencies will be explored and resolved. The lead investigator will be responsible for overseeing trial safety and ensuring that the best interests of participants are observed at all times. The lead investigator will be blinded to allocation, unless unblinding is deemed essential to ensure participant safety. Adverse events will be reported to the reviewing Human Research Ethics Committee and approved requirements.

An adverse incident is defined as a harmful, unpleasant, or undesirable response, reaction, or outcome experienced by a research participant or researcher. Adverse events that may be expected as part of the interventions or usual care that do not need to be reported to the HREC include, muscle soreness, swelling, or muscle cramps related to commencement of unaccustomed exercise or trips and/or falls, that have not resulted in an injury. A serious adverse event is defined as an event that may result in death, be life-threatening, require or prolong inpatient hospitalization, result in persistent or significant disability/incapacity, is a congenital anomaly or birth defect, is some other important medical event, and is expected or unexpected.

The collected data will be accessible only to the lead investigator and a few designated members of the research team. Since the intervention is deemed safe and poses minimal risk to participants, there may not be a requirement for interim analysis in this study. However, a safety monitoring plan will be strictly adhered to as outlined.

